#### Duration of cardiopulmonary bypass

The duration of cardiopulmonary bypass during the cardiac surgery.

#### Other variables

Will be collected through the analysis of the patient’s medical records, including the type of surgery, personal history, pre-operative ejection fraction, BMI, gender, and age.

*Adherence*. During the assessment and daily sessions, therapists will be instructed to raise awareness, provide guidance, and explain the purpose of the research to ensure maximum adherence to the protocol. Adherence assessment will involve direct communication between the researcher and the participating physiotherapists and students, facilitated through a dedicated messaging app group created for this purpose. Monitoring adherence will also include regular visits by the researcher during the application of the protocol treatment.

*Concomitant care*. Patients requiring extended ICU stays with the use of more advanced devices for prolonged non-invasive ventilation or even the return to invasive mechanical ventilation during the study period will be considered non-adherent from that point, and thus an intention-to-treat analysis will be employed.

*Risks and adverse effects*. Throughout the treatment, there are minimal risks of cardiac arrhythmias, decreased oxygen saturation levels, shortness of breath, bronchospasm, dizziness, syncope, hypotension or hypertension, altered heart rate, or chest pain. Throughout the entire duration, patients will be continuously monitored for vital signs.

#### Intervention protocol

The following training protocols will be applied.

*Control group (Usual physicaltherapy)*. Patients undergo physiotherapy treatment twice daily, transitioning from the ICU to the ward. In detail, the daily sessions are divided based on the days and settings, taking into account that patients are generally discharged from the ICU on Day 2 post-operation and that Day 1 represents the first day of post-operative care:

### DAY 1 (ICU)

Diaphragmatic breathing exercises – 1 set of 10 repetitions

Cough stimulation

Diaphragmatic breathing exercises combined with upper limb movements – Shoulder flexion/extension 2 sets of 10 repetitions up to 90 degrees

Diaphragmatic breathing exercises combined with lower limb movements – Thigh flexion 1 set of 10 repetitions, Dorsiflexion/plantar flexion 1 set of 10 repetitions

### DAY 2 (ICU)

Diaphragmatic breathing – 1 set of 10 repetitions

Cough stimulation

Diaphragmatic breathing exercises combined with upper limb movements – Shoulder flexion 2 sets of 10 repetitions

Diaphragmatic breathing exercises combined with lower limb movements – Thigh flexion 1 set of 10 repetitions, Dorsiflexion/plantar flexion 1 set of 10 repetitions

Cycle ergometer for 3 minutes

Breathing exercise with SMI (Strength Measuring Instruments) – 1 set of 10 repetitions

### DAY 3 (WARD)

Diaphragmatic breathing – 1 set of 10 repetitions

Cough stimulation

Diaphragmatic breathing exercises combined with upper limb movements – Shoulder flexion 2 sets of 10 repetitions

Diaphragmatic breathing exercises combined with lower limb movements – Thigh flexion 1 set of 10 repetitions, Dorsiflexion/plantar flexion 1 set of 10 repetitions

Ambulation (walking) for 5 minutes

### DAY 4 (WARD)

Diaphragmatic breathing – 1 set of 10 repetitions

Cough stimulation

Ambulation (walking) for 10 minutes

### DAY 5 (WARD)

Diaphragmatic breathing – 1 set of 10 repetitions

Cough stimulation

Ambulation (walking) for 15 minutes

*CPAP + Usual physicaltherapy*. They will be submitted to the same care as the control group, adding NIV with nasal CPAP 10cmH2O for 1 hour using device and brand approved by ANVISA, during the 5 days of hospitalization, both in the ICU and in the ward. The frequency of the sessions will be two (2) per day, in the morning and in the afternoon. Flexibility of time for carrying out the procedure is also planned, since in a hospital environment the patient can often undergo exams, other behaviors that may make it difficult to apply the protocol at the initially scheduled time.

*BIPAP + Usual physicaltherapy*. They will undergo the same care as the control group, adding NIV with nasal BIPAP with IPAP of 13cmH2O and EPAP 8 cmH2O for 1 hour, using equipment and brand approved by ANVISA, during the 5 days of hospitalization, both in the ICU and in the ward. The frequency of the sessions will be two (2) per day, in the morning and in the afternoon. Flexibility of time for carrying out the procedure is also planned, since in a hospital environment the patient can often undergo exams, other behaviors that may make it difficult to apply the protocol at the initially scheduled time. After the fifth day, the patient will be reassessed with the same instruments reported.

### Statistical analysis

The data will be analyzed using IBM SPSS Statistics Base 25.0 software for Windows. The normality of variables will be assessed using the Shapiro-Wilk test. The paired Student’s t-test will be utilized to compare data before and after the intervention. Linear Mixed Effects Models will be used for longitudinal data analysis. The effect of NIV (CPAP or BIPAP) combined with usual physiotherapy over time will be compared between groups using generalized linear mixed models (GLMMs), they can account for the correlation between repeated measurements within the same individual, which is important in longitudinal studies. The intention-to-treat (ITT) approach will be used to handle potential missing data. Time dependence is a key consideration in data analysis, and autoregression, particularly Integer Auto Regressive (INAR) models, is a valuable method for modeling this. However, selecting the appropriate autoregressive model is essential for gaining insights into the temporal dynamics of medical outcomes. Fixed effects models as a choice for addressing endogeneity. We use technique Bayesian model averaging to select relevant variables while controlling for overfitting. To ensure analysis accuracy, parametric model assumptions, such as homoscedasticity and residual normality, will be checked. Moreover, various models will be considered to accommodate specific data characteristics, such as skewness and zero-inflation/overdispersion.

Effect sizes will be calculated using Cohen’s d. Continuous variables will be reported as mean ± standard deviation (SD) along with a 95% confidence interval (CI), while categorical variables will be presented as absolute frequencies and percentages. The significance level will be set at 5% for all analyses (p ≤ 0.05).

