**Methods and analyses:**

This randomized, controlled, double-blind (patient and analyst) clinical trial will be conducted at Hospital João XXIII in Campina Grande, Paraíba, Brazil. Patients do not know which group they are allocated to. Those in the group that use CPAP or BIPAP will not be able to distinguish one from the other. The data analyst at the end of the collections will also be blinded. Only the health professional who will be applying the protocol cannot be blinded. The sample size, determined via sample calculation, yielded a total of 21 patients per group (63 patients). The patients will be allocated into 3 groups (CPAP group - CPAP + standard physiotherapy, BiPAP group - BiPAP + standard physiotherapy, and Control group - standard physiotherapy) in a 1:1:1 allocation ratio. The control group will receive the usual physiotherapeutic treatment as per the kinesiotherapy protocol. The treatment will be administered twice daily, starting in the ICU and progressing to the ward. In the CPAP group, nasal CPAP at 10cmH2O will be administered for 1 hour, twice daily, using an approved device. In the BiPAP group, nasal BiPAP with an IPAP of 13cmH2O and EPAP of 8cmH2O will be administered for 1 hour, twice daily, using an approved device. The NIV sessions will be conducted over the course of 5 days of hospitalization, both in the ICU and the ward. Assessments will be conducted at two time points: on day 1 preoperatively and on day 5 postoperatively. The following measures will be evaluated: pulmonary function, length of hospital stay, presence of postoperative pulmonary complications, score of the Minnesota Living with Heart Failure Questionnaire (MLHFQ) in its Portuguese version, functional capacity, the Global Perception of Change Scale, and the Functional Independence Measure (MIF). The normality of variables will be assessed using the Shapiro-Wilk test. IBM SPSS Statistics Base 25.0, using the Shapiro-Wilk test for normality and paired Student’s t-test for pre-post intervention comparison. They will use linear mixed effects models for longitudinal analysis and GLMMs to compare NIV effects over time between groups. They will employ ITT for missing data, INAR models for time dependence, fixed effects models for endogeneity, and Cohen’s d for effect sizes. Parametric model assumptions will be checked, and various models will be considered for data characteristics.

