### Post-randomization exclusion criteria

Undergoing hospital-based treatment contraindicating study participation (e.g., pacemaker implantation, pneumothorax requiring thoracic drainage).Death or other decompensations unrelated to the research.Return to the ICU.

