### Non-adherence to intervention criteria

Patient failing to complete 3 or more consecutive sessions.Patient voluntarily withdrawing from the study.Patient experiencing cardiac arrhythmia (atrial fibrillation, bradycardia) in two sessions despite medication and rest breaks.

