### Non-retention criteria

Patient not completing any of the follow-up evaluations.

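### Intention-to-treat is named as the missing-data method but supplies nothing for a patient without postoperative spirometry, and the withdrawal and post-randomisation exclusion rules do not fit with it

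*Protocol article*

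**What the plan says.** **Missing data.** The Statistical analysis section states: "The intention-to-treat (ITT) approach will be used to handle potential missing data". The Methods and analyses part of the abstract says the same: "They will employ ITT for missing data".

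**Non-adherence.** The criteria for non-adherence to the intervention include "Patient failing to complete 3 or more consecutive sessions" and, in the same list, "Patient voluntarily withdrawing from the study".

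**Non-retention.** A separate heading defines this as "Patient not completing any of the follow-up evaluations". No consequence is attached to the label.

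**Exclusion after randomisation.** The list covers contraindicating hospital treatment, death or other decompensation unrelated to the research, and "Return to the ICU".

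**Concomitant care** (under Other variables). Patients with an extended ICU stay on prolonged non-invasive ventilation, or who go back to invasive ventilation, "will be considered non-adherent from that point, and thus an intention-to-treat analysis will be employed".

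**Measurement and models.** The Interventions section plans one preoperative and one postoperative evaluation for included patients. The CPAP and BiPAP sections schedule the reassessment after the fifth day. Neither sets an adherence condition. The Statistical analysis section plans a paired t-test for before-and-after data, and linear and generalised linear mixed models for the longitudinal and between-group analyses.

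**The concern.** Intention-to-treat is a rule about the analysis set. A patient with no postoperative spirometry stays in the allocated arm under it, but the outcome is still absent. A reader of the article would think missing data had been dealt with.

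The status rules add to the difficulty. Someone who declines further sessions can usually still be measured; someone who withdraws from the study may not be. Listing both as non-adherence blurs the one distinction that decides whether the primary spirometry can still be obtained. Removing randomised patients after return to the ICU is also at odds with the label intention-to-treat.

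At stake is the comparison of FEV1 and FVC. Mask refusal is a route to loss that exists only in the two NIV arms. If patients who refuse the mask also have worse lung function and go unmeasured, the NIV arms would look better than they are.

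**Working it through.** The plan gives no loss rate, so there is no figure of its own to reproduce. The check is to run patient types through the stated rules, then see what the planned models can and cannot repair.

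**1. Patient types against the rules**

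| Patient | Status under the protocol | What intention-to-treat settles | Postoperative FEV1/FVC |
|---|---|---|---|
| Stops sessions, attends day 5 | Non-adherent, retained | Arm | Observed |
| Stops sessions, not seen on day 5 | Non-adherent and non-retained | Arm | Absent; no rule supplies it |
| Withdraws from the study | Listed as non-adherent | Arm | Not settled by the label |
| Leaves the ICU, then returns to it for invasive ventilation | Excluded after randomisation, and also non-adherent and kept under intention-to-treat | Contradictory | Not settled |

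The second row shows that the missing-data sentence has no effect. The fourth shows the direct contradiction between the exclusion list and the Concomitant care paragraph.

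**2. Bias in a raw completer mean**

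Let *m* be the fraction of an NIV arm without a day-5 value and *g* the amount by which those patients' mean lies below the observed mean. The full-arm mean is (1 − m) × observed + m × (observed − g) = observed − m × g, so the completer mean is too high by m × g. All inputs below except the 21 per group are assumptions:

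- 3 of 21 lost, g = 10 points of % predicted FEV1: 3/21 × 10 = 1.4 points.
- 6 of 21 lost, same g: 6/21 × 10 = 2.9 points.
- In SD units: m = 10%, g = 0.5 gives 0.05 SD; m = 20%, g = 1 gives 0.20 SD.

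These apply to a completer mean with no loss in control. They are not the bias of the planned mixed model.

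**3. What baseline adjustment repairs**

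A large-sample simulation used no true effect, a baseline to day-5 correlation of 0.6, no loss in control, and about 21% of day-5 values missing in one NIV arm, with lower values more likely to be lost. All of these are assumptions. A baseline-adjusted analysis stands in for a mixed model that keeps the preoperative value.

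| Loss depends on | False NIV benefit, completers | False NIV benefit, baseline-adjusted |
|---|---|---|
| Observed preoperative value | 0.11 SD | about 0.00 SD |
| Unseen day-5 value | 0.18 SD | 0.12 SD |

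The planned models can remove the first kind of bias and only part of the second. The paired t-test needs both measurements, so it uses completers only.

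**4. Which primary outcome is exposed**

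Pulmonary function needs the postoperative visit. Length of stay is a count of hospital days up to two weeks after randomisation and can be recorded without it.

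**The case against.** The strongest reply is that the text does not plan any loss. Non-adherence and non-retention have separate headings, so a patient who misses sessions but attends day 5 is already distinguishable from one who is never seen again. The reassessment is scheduled without an adherence condition, and the Concomitant care paragraph keeps one non-adherent group in the analysis. This stands. A reader might infer that patients who stop NIV lose their day-5 measurement, but no section says so. What is lacking is an express statement that measurement continues regardless of adherence.

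A reader might also infer that nothing would correct for such loss. That is not supported either: the planned mixed models give valid estimates when loss depends on observed data. The protection is partial, not absent.

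Nor can the bias figures be read as estimates. Control patients can also miss physiotherapy or withdraw, and patients who feel well may decline a mask, so both the imbalance and its direction are assumed.

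The non-retention wording is not an error in itself. It can refer to several instruments or time points, and no exclusion follows from it.

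Finally, an analysis plan that is not shown may hold the detailed missing-data methods. Their absence from the article is therefore not the finding. The wrong sentence, stated twice, the misplaced withdrawal item and the contradictory exclusion rule are in the article and need correction whatever such a plan contains.

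**Conclusion.** The point holds in limited form. Three things are wrong on the face of the protocol: intention-to-treat is given as a missing-data method, study withdrawal is filed under non-adherence to the intervention, and the post-randomisation exclusions conflict with intention-to-treat and with the Concomitant care paragraph.

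The consequence is a possible, not a planned, loss of FEV1 and FVC that could differ between the NIV arms and control. The documents do not allow its size to be estimated. Under the assumptions shown, a completer mean would be off by 1.4 to 2.9 points of % predicted FEV1. A baseline-adjusted comparison would be off by between about 0.00 and 0.12 SD, depending on what drives the loss. Length of stay is not affected by this route. The correction should be made, but the defect does not invalidate the design.

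**What to change.** - Replace the missing-data sentence, in the abstract and in the Statistical analysis section, with two statements. First, all randomised patients are analysed in their allocated arm. Second, missing postoperative spirometry is handled by the planned likelihood-based mixed model including the preoperative value, under missing at random.
- Add one sensitivity analysis that assigns less favourable values to patients who stopped NIV early and have no day-5 value.
- Move study withdrawal out of the non-adherence list, and record stopping sessions separately from withdrawing consent for further data.
- State that the day-5 assessment is sought regardless of adherence.
- Reconcile the post-randomisation exclusion list with the Concomitant care paragraph and with the intention-to-treat statement.

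The cost is wording changes and one extra analysis. No visit is added, because the postoperative assessment is already scheduled.

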### Interventions

The intervention will initially take place in the specific ward that receives cardiac surgery patients. Participant recruitment will begin upon the patient’s admission the day before the surgery, during which they will undergo a pre-operative assessment based on the study criteria.

Physiotherapists and physiotherapy students will receive training regarding the research protocol through two in-person sessions comprising demonstrations and didactic materials. The same therapists will be responsible for both the intervention and control groups.

Patients included in the study will undergo evaluations at two time points: pre-operatively (initial assessment) and post-operatively (five days after the pre-operative assessment).

Following the initial assessment, the patient will undergo cardiac surgery the next day and will be transferred to the ICU after the procedure. The protocol will be initiated in the ICU for all three groups of the research.

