#### Pulmonary function

All participants will undergo an evaluation by a CONTEC model spirometer (SPB80b, CHINA) to verify lung volumes and capacities. At least three tests will be performed, with a variation of less than 5% and the highest value obtained in one of the tests will be compared with the predicted values of pulmonary function parameters for the Brazilian population. FEV1 and FVC will be assessed. The predicted values will be calculated using the reference values [17].

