#### Gasometric data

Includes pO2 (partial pressure of oxygen), pCO2 (partial pressure of carbon dioxide), HCO3 (bicarbonate), Arterial Oxygen Saturation (SaO2), and Base Excess (BE). These measurements will be collected on Day 1 and Day 2, following the ICU routine and based on the patient’s clinical needs.

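### INAR models and an endogeneity correction do not fit a randomised trial with two assessments per patient, and the model-averaging step does not protect the arm terms or the baseline value

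*Protocol article*

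**What the plan says.** The Statistical analysis section first names paired t-tests for before-after comparisons, linear mixed models, and generalised linear mixed models (GLMMs) for comparing the groups over time. It then adds three further methods:

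- For dependence over time: "autoregression, particularly Integer Auto Regressive (INAR) models, is a valuable method for modeling this".
- "Fixed effects models as a choice for addressing endogeneity".
- "We use technique Bayesian model averaging to select relevant variables while controlling for overfitting".

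The Abstract (Methods and analyses) lists "INAR models for time dependence, fixed effects models for endogeneity" among the methods to be employed. It does not mention model averaging.

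On the data, the Abstract states: "Assessments will be conducted at two time points: on day 1 preoperatively and on day 5 postoperatively". The Interventions section agrees: "Patients included in the study will undergo evaluations at two time points". Under Pulmonary function, "FEV1 and FVC will be assessed". Under Length of hospital stay, the outcome is a number of days, capped at two weeks from randomisation. Blood gases are also limited to two days: "These measurements will be collected on Day 1 and Day 2, following the ICU routine and based on the patient’s clinical needs". Patients are randomised 1:1:1, 21 per group and 63 in all.

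**The concern.** The three added methods were made for other kinds of data. INAR models describe how a count at one time depends on counts at earlier times, so they need an integer series. Fixed-effects models for endogeneity come from observational panel data, where exposure may be related to unmeasured characteristics of the unit. Model averaging for variable selection lets the outcome data decide which terms enter, and with what weight.

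At stake is whether the plan can be carried out as written. One named method has no suitable primary outcome. One addresses a problem that the design has already removed. One could weaken the comparison the trial exists to make, unless the arm terms are protected.

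**Working it through.** **The plan's own figure.** The only computed figure is the sample size, 21 per group. The effect size and SD are not given, so it cannot be reproduced. For a two-sample comparison at two-sided 5% and 80% power, 21 per group implies a standardised difference of about 0.865 (0.85 needs 22 per group, 0.90 needs 20). The point does not depend on this figure. It serves below only as a benchmark effect.

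**INAR against the outcomes.**

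| Outcome | Type | Values per patient | Lags per patient |
|---|---|---|---|
| FEV1, FVC (primary) | continuous | 2 | 1 |
| Length of stay (primary) | integer days | 1 | 0 |
| Blood gases (secondary) | continuous | 2 | 1 |

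The primary outcome measured twice is not a count, and the primary outcome that is a count is measured once. With at most one lag per patient, there is also no basis for choosing between autoregressive models, a choice the section calls essential.

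**Fixed effects.** Assume patient intercepts (the unit is not stated), 63 patients and two visits.

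- Patient intercepts + time + two arm main effects: 63 + 1 + 2 = 66 columns. Each arm indicator is the sum of its own 21 patient indicators, so two columns are redundant and the rank is 66 − 2 = 64. Both arm main effects are lost.
- Patient intercepts + time + two arm-by-time terms: 66 columns, rank 66. The effect is estimable. In one simulated data set the estimates were 1.164 and 1.023, each with SE 0.256, identical to the between-arm differences in change score.

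With equal SD σ at both visits and correlation ρ between them, a change score has variance 2σ²(1 − ρ). The baseline-adjusted residual has variance σ²(1 − ρ²) = σ²(1 − ρ)(1 + ρ). The ratio is 2/(1 + ρ):

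- ρ = 0.3: 2/1.3 = 1.54
- ρ = 0.5: 2/1.5 = 1.33
- ρ = 0.7: 2/1.7 = 1.18

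The documents give no ρ, so these three values are assumptions.

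**Model averaging.** This was simulated under assumed settings: 21 per arm, the same true effect in both NIV arms, baseline correlation 0.6, outcome SD 1 within arm, four irrelevant covariates, BIC weights over all subsets of terms, and 200 runs per setting.

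| True effect (SD units) | Mean estimate, arm open to selection | Runs with arm inclusion probability below 0.5 | Mean estimate, arm in every model |
|---|---|---|---|
| 0.30 | 0.11 | 88% | 0.29 |
| 0.50 | 0.25 | 66% | 0.51 |
| 0.865 | 0.75 | 14% | 0.88 |

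The shrinkage comes from leaving arm open to selection. With arm retained in every model, it disappears.

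**The case against.** Several stronger readings are tempting, and the documents do not support them.

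- **Fixed effects remove the treatment effect.** Only the time-constant arm main effect is absorbed. The arm-by-time contrast survives and is a valid treatment effect in a randomised trial. It is close to the comparison over time that the section assigns to the GLMM. With complete data, an unconstrained arm-by-time mixed model gives the same change-score contrast, so the precision loss is not peculiar to fixed effects. It is the cost of not adjusting for baseline. That patient is the unit is itself an inference.
- **Two visits rule out model averaging.** They do not. It can be used on covariates if arm stays in every model. The variables to be selected may well mean covariates only, and a full analysis plan might say so. The section as written does not.
- **No method is assigned to the between-group comparison.** The GLMM is. The paired t-test has a different purpose, a linear mixed model is a special case of a GLMM, and the text does not direct every named method at one outcome.
- **INAR is impossible for every outcome.** The MLHFQ total is a score from 0 to 105 taken before and after, so a one-lag model pooled over patients is conceivable. It would say little about dynamics, and it is not a primary outcome.

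The defence also notes that INAR is called valuable, and fixed effects a choice, which is softer than a commitment. The Abstract, however, says both will be employed. It remains undisputed that INAR does not match either primary outcome and that randomisation leaves no endogeneity of arm to correct.

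**Conclusion.** The point holds in this form: the Abstract and the Statistical analysis section name methods that do not match a randomised trial with two assessments per patient. For INAR and the endogeneity correction, this follows from the document alone and needs no assumption.

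The precision cost, 1.18 to 1.54 times the variance of baseline adjustment, applies only if the fixed effects are per patient. It also assumes equal SDs at the two visits and a correlation between 0.3 and 0.7. The shrinkage under model averaging is conditional on arm being open to selection, and its size depends on the simulation settings. Under those settings an effect of the size the trial appears sized for falls from 0.865 to 0.75 on average, and smaller effects lose half or more. The problem should be corrected, but it does not undermine the trial: the GLMM comparison between groups stands apart from these sentences.

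**What to change.** 1. Delete the INAR and autoregressive text and the fixed-effects/endogeneity text, both in the Abstract (Methods and analyses) and in Statistical analysis.
2. In Statistical analysis, delete the model-averaging sentence, or confine it to a sensitivity analysis in which the arm terms and the baseline value are in every model.
3. State one prespecified primary between-arm model for FEV1 and FVC, with arm always retained and the baseline value as the fixed covariate.

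The cost is a small text change, with no new data and less analysis work. The Protocol modifications section rules out changes after registration, so the correction should be recorded as a dated clarification before unblinding.
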